## Abstract

**Background:**

Falls among older adults with intellectual disability (ID) are recognised as a serious health problem potentially resulting in reduced health-related quality of life and premature placement in residential care. However there are limited studies that have investigated this problem and thus falls rates among older adults with ID remain uncertain. Furthermore, people with ID rely heavily on familial and professional care support to address health problems, such as after having a fall. No studies have explored the post-fall care that people with ID receive.

**Method:**

This research will be carried out in two phases using a convergent mixed methods design. The aim of Phase 1 is to estimate the falls rate by prospectively observing a cohort of older adults (≥ 35 years) with ID (*n* = 90) for six months. Phase 1 will be conducted according to STROBE guidelines. In Phase 2, participants from Phase 1 who have experienced a fall(s) will be asked to participate in a semi-structured interview to explore their post-fall experience.

**Discussion:**

This study will determine the rate of falls among older adults with ID living in community based settings, which will assist to identify the extent of this problem. Data collected from the study will also aid in understanding the circumstance of falls and related falls risk factors in this cohort. This will include exploring any barriers that older adults with ID may encounter when seeking or undertaking recommended post-fall care advice. Findings from this research will potentially inform future development of falls prevention services for older adults with ID. This study has been approved by the University Human Research Ethics Committee.

**Trial registration:**

The protocol for this study is registered with the Australian New Zealand Clinical Trial Registry (ACTRN12615000926538) on 7 September 2015. www.anzctr.org.au/Trial/Registration/TrialReview.aspx?id=368990&isReview=true

## Background

Falls are a serious health problem which result in substantial socio-economic costs, with estimates that one third of people aged 65 years and over, who are living in the community, experience at least one fall per year [1, 2]. Falls are the leading cause of injury amongst older Australians [3]. In 2011–12 there were nearly 96,000 hospitalisations from falls related injuries in Australia, with each hospital stay lasting an average of eight days [3]. The healthcare cost associated with these falls was estimated to be $498.2 million in 2009 and this is expected to increase to approximately $1.4 billion by 2051 [4].

Falls among older adults with intellectual disability (ID) living in the community are also a cause for concern. People with ID have been observed to experience signs of ageing from their third decade in life [5, 6], and as such are considered ‘older adults.’ At least 50% or more of these falls result in injury [7, 8] and between 6 and 11% result in severe injuries, such as fractures and concussion [8, 9]. Qualitative research undertaken among adults with ID has found that falls may lead to reduced activity and independence and increase the burden of care on their caregivers [10]. Through observation, it has been suggested that people with ID have increased risk of institutionalisation from having falls [11]. Few studies have investigated falls rates amongst people with ID living in community based settings. Estimates range from 0.93 to 6.29 falls per person year [8, 9, 12, 13]. Other studies have reported between 25 and 40.1% of people with ID experienced a fall(s) during the observation period, but did not report the number of falls [7, 14–16]. Only three studies provided sufficient data to estimate injurious falls rates and these were 0.38–0.73 injurious falls per person year [8, 9, 13]. Research guidelines recommend reporting falls and injurious falls rates, as well as the proportion of people who fall when conducting falls related studies [16]. Additionally only one study implemented prospective daily recording of falls, [8] which is recommended for falls prevention trials [16] to ensure accurate and comprehensive collection of falls data. Limitations to these study designs, poses uncertainty about the extent of the problem of falls among older adults with ID. Additionally a limited amount of studies have investigated risk factors and preventive strategies for falls among people with ID [7, 12, 15]. A review which examined risk factors and preventative strategies for falls prevention in people with ID was only able to include seven studies, and found there was a lack of evidence about falls management for people with ID, prompting authors to recommend that more research in this area be undertaken [17].

It can be challenging to conduct robust research with older adults with ID [18] and conducting falls research with this group is no exception. There are ethical and legal considerations in gaining informed consent [19] and extensive adaptations are recommended to maximise the participation of people with ID [20]. Falls recommendations for older people have been developed from established evidence from large meta-analyses in the older community dwelling population [21], however these recommendations are not specifically applicable to people with ID [22]. The perspectives that older adults with ID have about falls and falls prevention services are also unknown, as there have been no studies which have sought to understand what experiences older adults with ID have when they fall and subsequently seek access to existing falls prevention services.

The primary aim of the study is to investigate the rate of falls in older adults with ID living in community based settings. The secondary aims of the study are to i) investigate the rate of injurious falls, ii) determine the risk factors for falls in this population, iii) explore the participant’s experience when seeking health services after having a fall, and iv) investigate barriers that participants may encounter when seeking to undertake evidence based falls prevention strategies that are recommended by the health service.

## Methods

### Design

A convergent mixed methods approach will be used in this study [23]. In Phase 1, a prospective observational cohort study will be conducted in accordance with STROBE guidelines [24]. In Phase 2, participants’ experiences of falls and access to falls prevention services will be explored using a descriptive phenomenological approach. Phenomenology is a research method used to describe a person’s lived experience of an event or ‘phenomenon’ [25]. In this case, it is the experience participants have when seeking healthcare services after a fall and the barriers that may be encountered while accessing or engaging in falls prevention recommendations. Data from the two phases will be analysed independently and the findings will subsequently be synthesised (Fig. 1).

**Fig. 1 Fig1:**
[figure not shown]
Participant flow through the study

### Ethics and informed consent

The study has received ethics approval from The University of Notre Dame Australia, Human Research Ethics Committee (015067F) and the affiliated local organisation for people with ID. All participants (or their legal representative or next-of-kin) will provide written informed consent to participate in the study. Three consent forms have been prepared: i) a consent form adapted to facilitate the participant’s understanding of the study and for what they are providing informed consent to, ii) a version for a family member or legal guardian to record their agreement for the person with ID to participate in the study and that in their opinion, the participant is not likely to object to participating in the study, and iii) a form for the caregiver(s) to provide informed consent that they are willing to support the participant with daily falls recordings and to facilitate communication with the researcher.

Ethical guidelines for research conducted in Western Australia (WA) contain information specific to adults who may lack the capacity to give consent [26]. These guidelines are also being followed when conducting this study. The guidelines specify that in accordance with the Guardianship and Administration Act [27], there is no provision for responsible persons to provide informed consent for a person who is assessed as being incapable of doing so, to take part in medical research [27]. Therefore in this study, where there is any uncertainty regarding the ability of the participant to provide consent, their guardian or next-of-kin will be asked to sign a separate consent form which records that they agree to the participant under their legal care participating in the study and that they believe the participant is not likely to object to participating in the study. Informed consent will be gained directly from the potential participant with ID where possible. The family member or caregiver will be asked to be present during this process to facilitate the participant’s understanding of what is involved in the study and witness the participant completing the consent form.

A step by step informed consent procedure will be carried out with each person with ID and their caregiver prior to determining if the person with ID is able to provide their own consent or if a proxy consent is required. The consent procedure consist of the researcher making several observations of the person with ID during the initial face to face meeting and during the discussion of the research. The researcher will ask the caregiver their opinion if the person with ID is able to make their own decisions. A short questionnaire is also administered to determine if the person with ID has understood the purpose of the study and the risk and benefits involved. The questionnaire will be administered in consideration of the communication style of the person with ID. The information gathered will allow the researcher to make a holistic informed decision regarding the person with ID’s ability to provide consent independently, or if a proxy consent is required.

After initial recruitment, the researcher maintains contact with the participant with monthly follow up, either by telephone or face to face, during the six month observational period. Telephone interviews are also conducted when the participant experiences a fall. These touch points provide an opportunity for the participant and the caregiver to raise any issues concerning data collection. It also provides the opportunity for the researcher to access the participant’s capacity to continue with the study and to seek verbal consent for continued participation. For participants providing consent independently, with their consent, the researcher will inform a suitable person who is involved in the participant’s care, to inform the researcher if there is a decline in cognitive function or health status. The researcher will follow with an assessment to determine their ability to provide consent and seek the legal representative for the participant where required, for continued participation.

In the later stages of the observation period, a caregiver who is involved in the care of a participant who experiences one or more falls may be asked to participate in an interview regarding their post-fall experience. Consent will be sought from the caregiver as well as the participant, for the caregiver to share their experiences with the researcher.

### Participants

People will be eligible for inclusion in the study if they have a confirmed diagnosis of ID or a diagnosis in which ID coexist, such as Down Syndrome, Retts Syndrome or Cerebral Palsy. People with ID in this study are defined by the Australian Psychological Society (APA), DSM – V criteria as people who present with limited intellectual and adaptive functioning [28]. This will be confirmed by their family or a caregiver. For the purpose of this project, adults with ID will be eligible if they are aged 35 years or older. Only older adults with ID living in the community will be eligible for inclusion. Community settings in Western Australia most often comprise of the older adult with ID living at home with their families, in independent units or in small group homes comprising of 2–9 housemates. Paid support caregivers are usually present for varying amounts of time within each living arrangement, to provide assistance with activities of daily living and community participation activities. Medical, allied health and social services are accessed through community options.

People with ID will be excluded if they are younger than 35 years old or living in a residential aged care facility such as a nursing home, or are in hospital. They will also be excluded from the study if they or their caregivers are unable to understand English.

### Setting and recruitment

Participants will be recruited from 2014 through to 2018, through a large non-for profit organisation that provides services to people with ID, operating in WA. This organisation provides an array of support services to over a thousand people with disability across the life span in the metropolitan and rural areas, including providing support with employment, accommodation, community participation, life-long learning and rehabilitation [29]. Approximately a quarter of the people for whom they provide services have a primary diagnosis of ID [30].

Participants will be recruited from advertisements and flyers posted on social media (Facebook and website) and within the common areas of the supporting organisation. Staff members of the organisation are also encouraged to provide study information to their eligible clients. Participants will be consecutively recruited until the target sample size of 90 participants is achieved. Participants who experience a fall in Phase 1 will be purposefully selected to participate in Phase 2 to ensure a diverse sample to capture data that will closely represent the experiences of older adults with ID when they seek healthcare services after experiencing a fall(s).

### Sample size

The incidence of falls in this population is uncertain, but based on previous studies is estimated to be about 0.27 [8, 12]. If the expected result is 0.27, we want 95% confidence, within a 1% absolute margin of error that the true incidence rate frequency lies between 0 and 1.27 [31]. Therefore a minimum sample size of 78 has been estimated to be required for Phase 1 of the study. As the study population has both physical and social disability and the observation period extends for six months, a drop out of approximately 15%, will be allowed for, which is higher than the 5% drop-out in a previous observational falls cohort study of older people [32]. Therefore the aim is to recruit 90 participants for Phase 1.

A purposeful sample [33] will be utilised for Phase 2. The aim is to purposefully select participants who have experienced a fall(s) in Phase 1 with different characteristics and/or consequences of the fall, in order to achieve a close representation of the experience older adults with ID have when accessing evidence based fall prevention recommendations. The aim is to be able to provide a holistic perspective about falls among people with ID and participants will be purposefully selected to represent those recruited. This sample will be guided by the participants who fall in Phase 1. Where possible, purposeful selection will include participants of different gender, age, diagnosis, level of independence and differing levels of communication (including verbal and non-verbal participants). Participants with different living arrangements (living with family or independently with or without support) and those who report varying circumstances surrounding their falls will also be considered when selecting the sample. Interviews will be continued until it is considered that saturation of themes has occurred [34] however it is understood that amongst this ‘hard-to-reach’ population this may not be entirely achievable.

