### Statistical analysis

#### Quantitative data analysis

Data will be analysed using the SPSS 23.0 software package (SPSS Inc., Chicago, IL, USA) and STATA 14.0 (StataCorp. 2015. Stata Statistical Software: Release 14. College Station, TX: StataCorp LP). Descriptive statistics will be used to describe the clinical and demographic characteristics of the participants. Falls analyses will follow recommended statistical guidelines for analysing falls data [32, 45].

The primary outcome measure (rate of falls) will be expressed as an incidence rate per person year. The number of participants who experienced a fall will be expressed as a percentage of people falling in the cohort. The rate of injurious falls will be expressed as the incident rate per person year. Generalised linear mixed modelling will be conducted to examine participant and their clinical characteristics predictive of falls, injurious falls and the risk of falling in the six months after commencement of the falls diary.

The modelling strategies will start with unadjusted univariate analysis, followed by multivariate analysis, adjusting for age, severity of ID, presence or absence of epilepsy, level of assistance required with activities of daily living, level of mobility and a history of falls in the six months prior to enrolment in the study. These variables have been shown to be predictive of falls in either older people or people with ID.

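### The sample size rests on an incidence of 0.27 with no unit or period; its stated inputs do not give 78, and no valid precision is shown for the primary outcome, falls per person-year

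*Protocol article*

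**What the plan says.** All places are in the protocol article.

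- **Sample size, planning value:** the incidence of falls is called uncertain but, "based on previous studies is estimated to be about 0.27 [8, 12"]. No unit or observation period is attached.
- **Sample size, precision:** "we want 95% confidence, within a 1% absolute margin of error", followed directly by the aim that "the true incidence rate frequency lies between 0 and 1.27 [31"].
- **Sample size, result:** "a minimum sample size of 78 has been estimated to be required for Phase 1 of the study". After that, "a drop out of approximately 15%, will be allowed for", so that "the aim is to recruit 90 participants for Phase 1".
- **Background, rates:** "Estimates range from 0.93 to 6.29 falls per person year [8, 9, 12, 13"]. The next sentence gives the share of people who fell as 25 to 40.1%, citing a different set of references (7 and 14 to 16).
- **Quantitative data analysis:** "The primary outcome measure (rate of falls) will be expressed as an incidence rate per person year". The percentage of participants who fall is a separate summary.
- **Outcome measures:** falls are recorded daily for six months, so each completer contributes 0.5 person-years.

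**The concern.** The primary aim is a rate of recurrent events. Its precision depends on the person-time observed, on the rate itself, and on how much fall counts vary between people. A planning value without a unit cannot be carried into such a calculation. This one also cannot be matched to the protocol's own summary of the literature, although references 8 and 12 are cited in both places.

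The margin, the interval and the sample size printed beside it do not fit one another, so a reader cannot recover how 78 was obtained. At stake is the justification for the size of Phase 1. The Discussion promises robust data on the falls rate, but the document gives no usable statement of how precisely that rate will be estimated.

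**Working it through.** **Inputs.** Planning value 0.27, 95% confidence (z = 1.96), margin 0.01, interval 0 to 1.27, N = 78 and 15% dropout (Sample size); 0.93 to 6.29 falls per person-year (Background); six months of follow-up (Outcome measures). The dispersion values in step 4 are assumptions; the documents give none.

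**1. Trying to reproduce 78.**

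As a proportion, n = z² p(1 − p)/d², with z² p(1 − p) = 3.8415 × 0.27 × 0.73 = 0.757:
- d = 0.01, as stated: 0.757/0.0001 = 7,571.5, so 7,572.
- d = 1.00, which the upper limit implies (1.27 − 0.27): 0.757, so 1.
- d = 0.10, not stated anywhere: 75.7, so 76. Conversely, at n = 78 the half-width is 1.96 × √(0.1971/78) = 0.0985.

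As a Poisson rate, n = z² × rate/(d² × t), with t the years observed per person:
- d = 0.01: about 10,372 (t = 1) or 20,744 (t = 0.5).
- d = 0.10: 104 (t = 1) or 208 (t = 0.5).
- d = 1.00: 2 (t = 1) or 3 (t = 0.5).

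The stated inputs do not give 78 on either scale. The nearest reading with a round margin is a proportion of 27% ± 10 percentage points.

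**2. The interval.** A value of 0.27 ± 0.01 would run from 0.26 to 0.28. An upper limit of 1.27 equals 0.27 + 1.00, and a proportion cannot exceed 1.

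**3. Matching 0.27 to the Background.**
- Per person-year: 0.27 is below 0.93.
- Per six months: 0.93 × 0.5 = 0.465 and 6.29 × 0.5 = 3.145, so 0.27 is again below the range.
- The two would agree at the lower end only over 0.27/0.93 × 12 = 3.5 months, a period the article does not mention.

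**4. Precision of the primary outcome with 78 completers.** Person-years: 78 × 0.5 = 39. With μ = rate × 0.5 and variance μ + kμ² (k = 0 is Poisson), half-width = 1.96 × √(variance/78)/0.5.

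| Rate per person-year | Expected falls | k = 0 | k = 1 | k = 2 | k = 4 |
|---|---|---|---|---|---|
| 0.93 | 36.3 | ±0.30 (33%) | ±0.37 | ±0.42 | ±0.51 (55%) |
| 6.29 | 245.3 | ±0.79 (13%) | ±1.60 | ±2.13 | ±2.90 (46%) |

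Worked case, rate 0.93 and k = 4: μ = 0.465; variance = 0.465 + 4 × 0.2162 = 1.330; 1.96 × √(1.330/78)/0.5 = 0.51.

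**5. Dropout step.** The target of 90 matches 78 × 1.15 = 89.7. Dividing instead gives 78/0.85 = 91.8, so 92. The difference is small and is not part of this point.

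**The case against.** The strongest reply is that 0.27 and 0.93 to 6.29 may be different quantities. If 0.27 is a proportion of fallers, or a rate over a shorter period, both figures can be true. That stands. A reader might infer that the planning value contradicts the literature outright, being 3.4 times (0.93/0.27) too low at one end and 23 times (6.29/0.27) at the other. Those ratios assume a shared unit that the Sample size section never states. The range also comes from four sources, so 6.29 cannot be attributed to references 8 and 12. What those two report cannot be checked from the article.

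Nor is it proven that 78 came from a proportion formula. The article names no formula, the match is 76 rather than 78, and it requires replacing the stated margin. A margin chosen to fit can produce 78 on another scale: a Poisson rate with margin 0.115 and a full year per person gives 78.4. That margin and that follow-up are not in the plan.

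Finally, Phase 1 is a descriptive cohort, and its observed confidence interval will show the precision achieved whatever the planning paragraph says. That also stands: no bias in the estimate is shown. None of this supplies the missing unit or makes the margin, the interval and N agree.

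**Conclusion.** The sample-size basis is wrong as written. The planning value has no unit or period and cannot be matched to the Background on either natural time scale. The 1% margin, the interval 0 to 1.27 and N = 78 are mutually incompatible, and this part needs no assumption about what the cited sources say. No valid precision is therefore shown for falls per person-year.

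A reader might go on to conclude that the study is too small. The document does not support that: it sets no target precision for the rate against which 78 or 90 could be judged. What can be said is that 39 person-years give a relative half-width of about 33% to 55% at the low end of the Background range and 13% to 46% at the high end. The lower figure in each pair is Poisson; the upper rests on an assumed negative-binomial dispersion of 4. All assume that 78 people complete six months.

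**What to change.** Rewrite the Sample size paragraph for Phase 1:

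1. State the unit and observation period of 0.27 and reconcile it with the rates in the Background.
2. Correct or remove the 1% margin and the 0 to 1.27 interval, so that the inputs shown lead to the N shown.
3. State the expected 95% confidence-interval half-width of the falls rate for 78 completers (39 person-years) across 0.93 to 6.29 falls per person-year, allowing for overdispersion over a stated range of dispersion values. The table above can serve as a start.
4. If 0.27 is kept as a proportion of fallers, label it so, give its margin as about ±10 percentage points, and cite studies that report proportions.

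The cost is one paragraph and no additional participants. The downside is that the stated precision becomes less favourable.

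### The sample-size statement contradicts itself: 0.27 with a 1% margin is 0.26 to 0.28, not 0 to 1.27, and 78 participants do not follow from it on any scale

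*Protocol article*

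**What the plan says.** The Sample size section of the protocol article takes an incidence that "based on previous studies is estimated to be about 0.27", citing references 8 and 12. It continues "If the expected result is 0.27, we want 95% confidence" and completes that requirement as "within a 1% absolute margin of error that the true incidence rate frequency lies between 0 and 1.27". From this it concludes that "a minimum sample size of 78 has been estimated to be required for Phase 1". An allowance for dropout then brings the recruitment target to 90.

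Three other places bear on the point:

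- **Background:** earlier studies, including references 8 and 12, gave 0.93 to 6.29 falls per person-year. A separate set of studies reported that 25% to 40.1% of people fell.
- **Outcome measures:** falls are counted over six months.
- **Quantitative data analysis:** the primary outcome is reported as a rate per person-year.

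**The concern.** Four figures (0.27, 1%, 0 to 1.27, and 78) are presented as one chain of reasoning, but the interval does not match the margin and the sample size does not match either. The section also does not say whether 0.27 is a proportion of people or a rate of falls, and its wording mixes the two.

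This is the only justification given for the size of Phase 1 and the only precision target for the primary aim, which is to estimate the falls rate. As it stands, a reader cannot tell how precisely that rate will be known, and anyone reusing the calculation for a later study would carry the error forward.

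**Working it through.** **Inputs.** Expected value 0.27, confidence 95% (taken as two-sided, z = 1.96), margin 0.01, stated interval 0 to 1.27, stated minimum 78 (all from Sample size). Follow-up of six months (Outcome measures), so 78 people with complete follow-up give 78 × 0.5 = 39 person-years. Prior rates 0.93 to 6.29 per person-year (Background).

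**1. Interval against margin.** 0.27 − 0.01 = 0.26 and 0.27 + 0.01 = 0.28. The printed interval is 0 to 1.27. This step needs no assumption.

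**2. Trying to reproduce 78 with 0.27 as a proportion.** n = z²p(1 − p)/d².

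- n = 1.96² × 0.27 × 0.73 / 0.01² = 7,571.5, so 7,572. A one-sided z gives 5,333.
- With a finite-population correction, n is 243, 289 or 884 for populations of 250, 300 or 1,000. None is near 78.
- Half-width at 78: 1.96 × √(0.27 × 0.73 / 78) = 0.0985, or ±9.9 points (about 17% to 37%). If all 90 were followed it would be ±9.2 points.
- A proportion cannot reach 1.27.

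**3. Trying to reproduce 78 with 0.27 as a rate per person-year (Poisson).** Person-years = z² × rate / d².

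- Margin 0.01: 1.96² × 0.27 / 0.01² ≈ 10,372 person-years, or about 20,744 people for six months.
- Margin 1: 1.96² × 0.27 / 1² = 1.04 person-years, or two to three people. With the lower limit cut at zero, this margin does give 0 to 1.27, but not 78.
- Half-width from 39 person-years: 1.96 × √(0.27 / 39) = ±0.16 per person-year.

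**4. Other routes to 78.**

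| Reading | n | Fits 0 to 1.27? |
|---|---|---|
| 0.27% ± 1 point, no correction | 103.4, so 104 | yes, in percent, cut at 0 |
| 0.27% ± 1 point, corrected for a population of 250 | 73.4, so 74 | yes, in percent, cut at 0 |
| 0.27% ± 1 point, corrected for a population of 300 | 77.1, so 78 | yes, in percent, cut at 0 |
| 27% ± 10 points | 75.7, so 76 | no |

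The population of 300 is an assumption, and the section mentions no correction. Setting and recruitment describes over a thousand clients, about a quarter with a primary diagnosis of ID, which suggests roughly 250 or more.

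**5. Does 0.27 fit the Background?** As a yearly rate it lies below 0.93. As a six-month rate it would be 0.27 × 2 = 0.54 per year, still below 0.93. As 0.27% it would mean about one person in 370 (1 / 0.0027), against 25% to 40.1% fallers. As 27% it would fit the range for fallers, but references 8 and 12 are cited in the Background for rates, not for that range.

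**6. Precision on the primary scale at the Background rates, 39 person-years, Poisson.**

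- Rate 0.93: 1.96 × √(0.93 / 39) = ±0.30.
- Rate 6.29: 1.96 × √(6.29 / 39) = ±0.79.

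Repeat fallers make the counts more variable than Poisson. The half-width then grows by the square root of the variance-to-mean ratio.

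**The case against.** The best defence is that 78 may have a sensible origin that the article compresses. Two candidates come close. One is 0.27% ± 1 point with a correction for a population of about 300, which yields both 78 and the printed interval, and the recruiting organisation's client numbers make such a population plausible. The other is that 1% is a slip for 10%, which gives 76. The section also cites a source for its method, which is not available here.

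What stands is that the origin of 78 is unknown and may have been reasonable. Neither candidate rescues the text. The first needs a correction that is never mentioned and an incidence that the Background rules out. The second leaves 0 to 1.27 unexplained. No source could make 0.27 ± 0.01 equal 0 to 1.27.

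It is also fair to say that this is a descriptive cohort with no hypothesis test, that a confidence interval reported with the results would show the precision achieved, and that a careful reader who sees 0 to 1.27 in the same sentence may not come away believing ±1%. That limits the harm but does not make the statement right.

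Two stronger readings should be resisted. A reader might infer that the formula was definitely run with 0.0027, because the interval looks like percentages. But a rate of 0.27 ± 1 cut at zero gives the same interval, so this remains a guess. A reader might also take 0.27 as the expected share of people who fall. The article never says so.

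**Conclusion.** The precision statement is wrong as written. That the interval contradicts the margin rests on nothing but the printed figures. That 78 does not follow holds whether 0.27 is a proportion (7,572 needed, about 97 times 78; delivered margin about ±10 points) or a rate per person-year (10,372 person-years needed; delivered margin about ±0.16). The first set of figures assumes a simple binomial proportion. The second assumes Poisson counts and complete six-month follow-up of 78 people.

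A reader might infer from the factor of 97 that the cohort is far too small and must be enlarged. The article does not support that. A ±0.01 margin is not credible as the intended target when the same sentence prints 0 to 1.27, and a cohort of 78 to 90 can still give a useful estimate with an honest interval. The fault lies in the stated basis and precision, not demonstrably in the number recruited.

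**What to change.** Rewrite the paragraph:

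1. Delete the 1% absolute margin and the 0 to 1.27 interval.
2. State what 0.27 measures, over what period and in what unit, and reconcile it with the Background's 0.93 to 6.29 falls per person-year, since references 8 and 12 are cited for both.
3. State the precision that 78 completers deliver on the primary scale. Suitable content: 78 participants followed for six months provide 39 person-years; assuming Poisson counts, the 95% confidence interval has a half-width of about 0.30 falls per person-year at a true rate of 0.93 and about 0.79 at 6.29, and will be wider if falls cluster in repeat fallers.
4. If the proportion of fallers is also given, add that its half-width is about 10 percentage points at 27%.
5. If 78 did come from a finite-population correction or a 10-point margin, say so and give the inputs.

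The cost is one paragraph of rewording. Enrolment can stay as planned. The stated precision becomes less favourable than a 1% margin suggests.
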